## Recruitment process and measurements procedures

The evaluation protocol scheme is shown in Table 2. The measurements will be carried out in different days. The first assessment day will coincide with the 12th gestational week visit to the gynaecologist at “San Cecilio” University Hospital, Granada, and potential participants will be individually informed about the study objectives, evaluation protocol and procedures. If the woman agrees to participate in the present RCT, the researcher will provide detailed information about each of the phases of the study, and the participant will be asked to read and sign written informed consent. Subsequently (on the same day), weight and height will be assessed. On the second assessment day (16th gestational week) participants will attend the research centre and they will complete the following assessments: nutritional and clinical information, blood pressure, resting heart rate and physical fitness. The initial survey (anamnesis) will be conducted through face-to-face interviews by trained staff in order to gather data on sociodemographic characteristics, reproductive history, history of illness (hypertension, diabetes, obesity, etc.), and diet. Other health information will be collected using a self-administered questionnaire and it will include personal questions regarding smoking and alcohol habits and indicators of socio-demographic and socio-economic status (such as personal and household income, educational level or marital status). This survey will also include questions regarding the employment of nutritional supplements or special diets. Participant will then receive the accelerometer and questionnaires to be completed there or at home, and will be asked to return them eight days later. Additionally, the Hospital will make an appointment with the participants during that week for the biochemical and urine samples collection. The third day of evaluation will consist on accelerometry and sleep quality assessment on the 24th week of gestation. The fourth day of evaluation will take place on the 34th week of gestation. This evaluation will be exactly the same to that performed in the second day of evaluation before the exercise program started (i.e. 16th gestational week), including biochemical assessments.

**Table 2 Tab2:** Evaluation protocol scheme

	Criteria (12th week)	Baseline (16th week)	Second trimester (24th week)	Third trimester (34th week)	Delivery	1 month post-partum
Informed consent	X					

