1st day evaluation						
Sociodemographic data		X				
Clinical history		X		X	X	X
Weight and height	X	X		X		X
Body composition (dual-energy x-ray absorptiometry)						X
Accelerometry		X	X	X		
Physical fitness		X		X		
Nutritional study		X		X		X
Questionnaires to be fill there or at home between the 1st and 2nd evaluation days						
Low back-pain		X		X		X
Quality of life		X		X		X
Sleep quality		X	X	X		X
Physical activity		X	X	X		X
Self-perceived physical fitness		X	X	X		X
Sexual function		X		X		X
Restless legs syndrome		X		X		X
Mental and positive health		X		X		X
2nd day evaluation: Accelerometers collection and review of questionnaires		X		X		
Maternal biochemical analysis		X		X	X	
Umbilical cord blood sampling					X	
Maternal urine sampling		X		X	X	

Blood samples (5 mL) of all pregnant participants will be extracted at week 16th and 34th of gestation, and at delivery. Samples of venous and arterial blood from the umbilical cord (5 + 5 mL) at the time of delivery will be taken. In addition, samples of urine at 16 and 34 weeks gestation and delivery will be collected. All samples will be immediately frozen and conserved at −80 °C to avoid breaking the cold chain before being sent to the laboratory.

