## Sample size

The number of participants to be included in the study was calculated on the basis of the change in body weight. We used the difference in weight change observed between the control and intervention group (1.04 Kg) in Ruiz et al. [20] as the expected effect size. A total of 52 women (26 per group) will be needed to detect a mean group difference of 1.04 and a standard deviation of 1.15 Kg in weight change with a power of 90 % and α of 0.05. However, we will exceed this sample size to allow for withdrawals. Assuming a maximum lost-to-follow up of 15 % [20], we will recruit a total of 30 participants per group (*n* = 60).

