To maximize adherence, several strategies will be implemented including music in all sessions and telephone calls following missed sessions. The researchers will control and register the presence of adverse events during the class and between classes.

The participants randomly assigned to the control group (*n* = 30) will receive general advices about the positive effects of PA during pregnancy for her and the foetus’s health status. The researchers will give three seminar explaining 1) the benefits of exercise for a better pregnancy, prevention and treatment of GDM and excessive weight gain; 2) ergonomic advises, exercises to perform at home (e.g. stretching, resistance training) and strategies to increase their daily PA levels; 3) the benefits of the Mediterranean Diet and nutritional education. Moreover, we will prepare brochures describing the overall benefits of PA on health, and we will dispense general guidelines to increase the level of daily PA and optimum nutrition during pregnancy [63, 64].

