## Primary and secondary outcomes

### Primary outcome

The primary outcomes are maternal weight gain and maternal and foetal glycaemic profile. Maternal weight gain will be defined as the weight change from baseline measurement to the last measurement at 34th week of gestation. Maternal insulin sensitivity will be derived from the homeostatic model assessment for insulin resistance (HOMA-IR), which will be calculated using the formula [fasting insulin (μIU/mL) × fasting glucose (mg/dL)]/405 in the 34th week of gestation. Neonatal insulin sensitivity will be assessed through the cord blood ratio glucose/insulin.

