## Statistical analysis

Since this study aims at determining potential biological effects of exercise, the statistical analysis will be performed on a per-protocol basis, thus, including in the analyses only participants who attended at least 80 % the exercise session and completed both baseline and follow-up evaluations. The treatment effects will be reported as between-group changes on the primary and secondary outcomes and will be assessed with generalized linear models after adjusting for baseline values. All the analyses will be repeated additionally adjusting for age and any other confounder potentially not well balanced at baseline, and the results from both models will be reported. The effect size (95 % confidence interval) and statistical significance will be reported for each study outcome. The statistical significance will be set at α = 0.05. Sensitivity analyses will be conducted using intention-to-treat analyses and baseline observation carried forward imputation.

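### Baseline observation carried forward gives women without a week-34 weight a gain of 0 kg, a near-best score, so it is not a conservative check on maternal weight gain

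*Protocol article*

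**What the plan says.** Under Statistical analysis, the main analysis is per-protocol, "including in the analyses only participants who attended at least 80 % the exercise session and completed both baseline and follow-up evaluations". The checks on it are given in one sentence: "Sensitivity analyses will be conducted using intention-to-treat analyses and baseline observation carried forward imputation". The article gives no reason for this imputation and names no alternative.

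Under Primary outcome: "Maternal weight gain will be defined as the weight change from baseline measurement to the last measurement at 34th week of gestation". Table 2 places baseline at the 16th week. Its row "Weight and height" is marked at weeks 12, 16 and 34 and one month after delivery, but not at week 24. There is therefore no scheduled weight between baseline and the endpoint.

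The article treats less gain as better. The Background lists prevention of excessive gestational weight gain among the benefits of activity, and the control-group seminars under Exercise intervention cover "prevention and treatment of GDM and excessive weight gain". The Sample size section plans to "detect a mean group difference of 1.04 and a standard deviation of 1.15 Kg in weight change", with 90% power, 26 women per group, and 30 per group after allowing for at most 15% loss.

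**The concern.** Carrying the baseline forward is usually defended as cautious because a participant with no change is scored as having had no benefit. That defence fails for gestational weight gain. Pregnant women are expected to gain weight between weeks 16 and 34, and the intervention aims to make that gain smaller. A score of no change is then close to the best attainable result.

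The main analysis keeps only women who attended enough sessions and completed both evaluations. A reader will look to the sensitivity analyses to see whether that selection matters. If the only stated imputation depends on which arm lost more women, it can appear to confirm the per-protocol result or to contradict it for reasons unrelated to exercise.

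**Working it through.** **Inputs from the article.** Design difference 1.04 kg, SD 1.15 kg, α 0.05, power 90%, 26 per group raised to 30, maximum loss 15%. A two-sided test is assumed, as the article does not state sidedness.

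**Assumed input.** Mean control-arm gain μ from week 16 to week 34 of 6, 8 or 10 kg. The article gives no such figure.

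**The plan's own figure.** n per group = 2 × (1.960 + 1.282)² × 1.15² / 1.04² = 25.7, rounded up to 26, or 52 in total. This reproduces the plan; the sample size is not in dispute. With a t-test, 26 per group gives 89.2% power, and the 25.5 per group expected to remain from 30 after 15% loss gives 88.6%. Hence about 89% for completers.

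**The imputed value.** Week-16 weight minus week-16 weight = 0 kg. With the exercise mean 1.04 kg below control, zero lies (6 − 1.04)/1.15 = 4.3 SD below the exercise mean at μ = 6, and (10 − 1.04)/1.15 = 7.8 SD below it at μ = 10.

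**Formulas.** With the proportion d of an arm imputed as zero and true arm mean m:
- expected arm mean = (1 − d) × m
- arm variance = (1 − d) × SD² + d × (1 − d) × m²

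**Unequal loss, no true effect (20% exercise, 10% control).** Difference = 0.8μ − 0.9μ = −0.1μ, that is −0.6, −0.8 and −1.0 kg at μ = 6, 8 and 10. The shift favours exercise. Reversing the split reverses the sign.

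**Unequal loss the other way, true effect 1.04 kg (10% exercise, 20% control).** Difference = 0.9(μ − 1.04) − 0.8μ = 0.1μ − 0.94, that is −0.34, −0.14 and +0.06 kg. A real benefit almost or wholly disappears.

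**Equal loss, true effect 1.04 kg (15% in each arm).** Difference = 0.85 × (−1.04) = −0.88 kg at any μ. At μ = 6:
- exercise variance = 0.85 × 1.3225 + 0.1275 × 4.96² = 4.26
- control variance = 0.85 × 1.3225 + 0.1275 × 6² = 5.71
- root mean variance = 2.23 kg, against 1.15 kg planned
- standard error = √((4.26 + 5.71)/30) = 0.577
- power ≈ Φ(0.884/0.577 − 1.96) = 33%

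The same steps give 22% at μ = 8 and 16% at μ = 10. Simulation of 20,000 trials per setting, with each woman lost at random and a two-sample t-test on change, gives 33%, 23% and 17%. With exactly 4 of 30 missing in each arm, power is lower still: about 21%, 2% and under 1%.

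**False positives.** With no true effect and losses at random with probabilities 20% and 10%, the simulation rejects in 16% to 17% of trials. With exactly 6 of 30 and 3 of 30 missing, it rejects in about 1% or fewer. With equal 15% expected loss it stays near 5%.

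These calculations compare mean change directly and omit the planned adjustment for baseline.

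**The case against.** The strongest reply is that this is only a sensitivity analysis. The main result excludes women without follow-up, so carrying the baseline forward cannot change its estimate, its confidence interval or the sample size. That stands, and it limits the severity.

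The sentence can also be read as two separate analyses, one by intention to treat and one with imputation. The article does not settle this, so one cannot say that the intention-to-treat analysis necessarily rests on this imputation. It remains the only imputation named, and it misbehaves for weight gain under either reading.

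Some stronger readings are tempting but not supported:
- **Every woman who drops out scores zero.** Only women without a week-34 weight do. Those who stop exercising but are weighed keep their observed value, and those lost after week 34 already have the outcome. At 15% loss, 4 or 5 of 30 per arm are affected.
- **They become the best results in the trial.** A completer who lost weight would rank better, so near-best is the accurate description.
- **The method manufactures significant findings for exercise.** The direction depends on which arm lacks more weights. The 16% to 17% rejection rate comes from random variation in the number lost; at an observed split of 6 versus 3 the inflated variance holds rejection to about 1% or less.
- **The method is a further error for the neonatal outcome.** Cord-blood glucose/insulin has no baseline to carry, so the rule simply does not apply there. Handling by outcome can be left to a fuller document.

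**Conclusion.** The concern holds for maternal weight gain. The article's own definitions make the imputed gain 0 kg, and nothing else in the text corrects this. Each 10-point difference between arms in missing week-34 weights moves the estimate by a tenth of the mean gain: 0.6 to 1.0 kg if that mean is 6 to 10 kg, which is 58% to 96% of the 1.04 kg design effect. With equal 15% expected loss, the effect shrinks by 15% and most of the power goes.

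That the imputed gain is zero, and the 15% shrinkage under equal loss, need no assumption about mean gain. The sizes of the shift and of the power loss do depend on it, and the power figures also use the planned SD of 1.15 kg. The case rests on the shift in the estimate and the loss of power, not on false-positive rates.

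This should be fixed rather than must be fixed: it affects a sensitivity analysis, though the only stated missing-data check on a per-protocol main analysis.

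**What to change.** Remove baseline observation carried forward for maternal weight gain and state instead:

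1. All randomised women are analysed as allocated, using every observed week-34 weight regardless of session attendance.
2. Missing week-34 weights are multiply imputed from a small set of variables already collected, for example week-12 weight, week-16 weight, age and arm, and combined by Rubin's rules. With about 25 completers per arm the model must stay small. Session attendance should not be a predictor, because it has no counterpart in the control arm.
3. One simple sensitivity analysis assumes that exercise-arm women with missing weights gained like controls.

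The wording should also make clear whether intention to treat and imputation form one analysis or two. The change should be made before unblinding, because the direction of the present bias depends on which arm loses more women.

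The cost is a few sentences and a little more programming, with no new data. The drawback is that the multiple imputation relies on a missing-at-random assumption, which the third step probes only in part.

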## Discussion

This paper describes the protocol performed by a multidisciplinary team of experts in PA and exercise, nutrition, gynaecology and physiology that aims to determine the effects of a supervised exercise intervention developed in overweight and grade I obese pregnant on the mother and newborn health, and the influence of lifestyle during pregnancy on relevant, but no explored yet, maternal and foetal outcomes.

The intrauterine environment seems to be involved in programming and foetal offspring exposed to maternal stress, inappropriate diet, physical inactivity, obesity or hyperglycaemia, among others, may be prone to future metabolic alterations and chronic diseases [26, 89–91]. Among these modifiable behaviours, PA is especially relevant during gestation [4–6]. Increasing PA levels or exercising during pregnancy is an efficient tool to tackle cardiometabolic diseases such as GDM, and excessive maternal and neonatal weight gains [5, 19, 92]. However, modern society sometimes treats pregnancy as a disease. For example, it qualifies as vulnerable women and are excluded from most studies [93]. Furthermore, is noticeably that most of the interventions focus on improving pregnant health involve mere advices or counselling given face to face, or by phone (or both). Just few trials have investigated well-controlled individually tailored exercise interventions. Consequently, further trials, with objective outcome measures, are needed. Moreover, the influence of physical fitness on important maternal health markers during gestation, such as quality of life, positive health, inflammatory profile, bone health, or oxidative stress is unknown.

Exercise during pregnancy is safe [21, 22] and side-effects are minimal [53, 54] if pregnant adequate the intensity of such exercise to warrant foetal wellbeing [94]. However, the exercise intensity suggested by the ACOG in 2002 [53] and by Davenport et al. [95] will not be adopted in the present RCT. This is firstly, because the minimum work intensity is stated at 101 bpm for all women (which constitute a low heart rate), and secondly, because they make an absolute estimation (independently of the woman’s age, basal heart rate, or physical fitness status). Thereby, in agreement with Zavorsky & Longo [55], we advocate for modulating the intensity based on the % HRR, and the RPE.

Not less important for an optimal pregnancy is a healthy psychological status [31, 32, 96]. In that sense, exercise represent an excellent opportunity to improve quality of life [33] and reduce cortisol levels, which may in turn have a positively influence on the foetus and child [31, 32]. Besides, it is unknown whether exercise could positively influence the characteristic worse sleep quality during gestation [48, 49], which can alter the pregnant metabolic status [41–43] and gestational outcomes [44–46] and negatively affect the pregnant quality of life [37–40] and the foetal development [47].

There is a clear and compelling rationale for increased pregnancy research in order to address the therapeutic needs of pregnant women [93]. Additionally, there is accumulating evidence that pregnancy provides a unique window into understanding fundamental mechanisms underlying observed links between a pregnant woman’s health and her later health and the health of her children [93]. The information obtained from this RCT will therefore be of clinical and public health interest and will suggest future research. Further, the exercise intervention designed is novel and non-expensive, and can be easily transferred to other similar contexts. Consequently, the findings of the GESTAFIT Project will help the Health Systems to identify strategies for primary prevention and health promotion among overweight and obese pregnant.

## Abbreviations

GDM: Gestational diabetes mellitus
HRR: Heart rate reserve
PA: Physical activity
RCT: Randomised controlled trial
RPE: Rate of perceived exertion
SD: Standard deviation
VO_2max_: Maximal oxygen uptake
